### Follow-up and assessments

The assessments and follow-up schedule (with a window period of ±2 months) are summarised in Table 1.

**Table 1 Tab1:** Summary of study procedures and schedule

Study procedures	Visit 1	Visit 2	Visit 3
	Screening/Baseline	Month 6	Month 12
Informed consent	x		
Assess eligibility	x		
SMAQ	x	x	x
BMQ, ASK-12	x		x
Prescription data	x	x	x
Pill count and refill data		x	x
Estrone, estradiol and androstenedione assays	x		x
UPIRTSO event		x	x
Patient log of daily pill taken and weekly SMS		x	x
^a^Check receipt of SMS	x	x	x

^a^Research coordinator will verbally check the status of SMS receipt at each clinic visit

The patients will be followed up half yearly. The SMAQ will be administered at each visit, while the BMQ and ASK-12 questionnaires will be administered at baseline and 1-year. The hormone assays of estrone, estradiol and androstenedione will also be performed at baseline and 1-year.

This trial does not involve any experimental treatment and thus poses no additional risks to patients. Nevertheless, at each follow-up visit, the research coordinator will record any symptom or event that a patient may have experienced that is considered as UPIRTSO (Unanticipated Problems Involving Risks to Subjects and Others) event. These events will be monitored closely using a log book.

### Statistical considerations

#### Sample size

The sample size is estimated based on the primary endpoint of medication adherence (as measured via SMAQ) at 1-year. Assuming that the proportion of medication adherence in the intervention and control groups are 80 and 60% respectively, [17] then based on a 5% significance level and a power of 90%, a minimum sample of 240 subjects (i.e. 120 per group) will be required. Further assuming an attrition rate of 10%, the overall trial size is 280.

#### Statistical analysis plan

The assessment of medication adherence at 1-year between the SMS reminder and control groups will be made using the χ^2^ test, with adjustment for potential confounders made using the logistic regression.

Natural log transformation will be implemented on the estrone and androstenedione measures to normalise the data. The comparison of secondary outcomes involving estrone and androstenedione levels will be made using the analysis of covariance (ANCOVA) to adjust for the respective baseline levels and other potential confounders. The estradiol levels (defined as < 18.4 pmol/L versus ≥18.4 pmol/L) will be compared between the two arms using the χ^2^ test and the logistic regression analysis will be implemented to adjust for baseline covariate and other potential confounders where appropriate.

The assessment of knowledge, attitude, behaviour, as well as barrier and facilitating factors between the intervention and control groups will be made using χ^2^ tests, with treatment effect quantified based on odds ratio estimate and its 95% confidence interval. Further adjustment for baseline scores and other potential confounders will be made using the logistic regression analysis where appropriate.

All analyses will be performed according to the principle of intention-to-treat using STATA version 15, assuming a two-sided test at the 5% level of significance.

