### Randomisation procedure

All eligible patients who have provided informed consent will be randomised to receive either SMS reminder or standard care in a 1:1 ratio. Balanced permuted block randomisation will be implemented with varying block sizes, stratified by centre. Allocation concealment will be ensured, as the randomisation allocation, generated by the responsible statistician, will not be released to the research coordinator until the patient has been recruited into the trial by means of a central telephone call upon meeting the eligibility criteria. The study flow chart is shown in Fig. 2.

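### The primary comparison is an unadjusted chi-square that uses neither centre nor baseline SMAQ; a pre-specified logistic model with both would be a nearly free improvement

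*Protocol article*

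**What the plan says.** **Primary analysis.** The Statistical analysis plan section of the protocol article tests adherence at 1 year with a chi-square, "with adjustment for potential confounders made using the logistic regression". The covariates are not named. The abstract gives the same pair of methods but says the logistic model adjusts for a baseline covariate as well as confounders.

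**Other outcomes.** The same section names baseline adjustment for estrone, androstenedione, estradiol and the questionnaire scores.

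**Design.** Under Randomisation procedure: "Balanced permuted block randomisation will be implemented with varying block sizes, stratified by centre". Under Follow-up and assessments: "The SMAQ will be administered at each visit, while the BMQ and ASK-12 questionnaires will be administered at baseline and 1-year". Baseline SMAQ is therefore scheduled for every participant.

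**General rules.** "All analyses will be performed according to the principle of intention-to-treat using STATA version 15", "assuming a two-sided test at the 5% level of significance".

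**Sample size.** The assumption is that "the proportion of medication adherence in the intervention and control groups are 80 and 60% respectively". The calculation is "based on a 5% significance level and a power of 90"%, giving "a minimum sample of 240 subjects (i.e. 120 per group) will be required".

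**The concern.** Three things in the document do not fit together well.

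1. Centre shapes the randomisation but is named in no analysis of any outcome.
2. In the body text the primary endpoint is the only efficacy outcome without a named baseline adjustment. Baseline SMAQ is the same instrument taken one year earlier, so it is a natural candidate for a strong predictor. The abstract appears to include it.
3. Two tests of the primary endpoint are planned. Which one is primary has to be inferred from word order and from the sample size calculation.

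At stake are some power and, in an open-label trial, some room to choose between two results after seeing the data. The choice of unnamed confounders adds to that room.

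**Working it through.** **Step 1: reproduce the planned sample size.** Inputs from Sample size: p1 = 0.80, p2 = 0.60, difference d = 0.20, two-sided 5% (z = 1.960), 90% power (z = 1.282). The mean proportion is 0.70.

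n = [1.960 × √(2 × 0.70 × 0.30) + 1.282 × √(0.80 × 0.20 + 0.60 × 0.40)]² / d²
= [1.960 × 0.648 + 1.282 × 0.632]² / 0.04
= 2.081² / 0.04 ≈ 108.2, so 109 per arm.

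With continuity correction: n' = (n/4) × [1 + √(1 + 4/(n × d))]² ≈ 118.0 from the unrounded n (118.8 from n = 109), so 119 per arm, or 238 in total. The stated 240 is reproduced. The trial is sized on an unadjusted two-proportion test.

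**Step 2: power of the chi-square as planned.** With 120 per arm, without continuity correction:

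Φ{[0.20 × √120 − 1.960 × 0.648] / 0.632} = Φ{(2.191 − 1.270) / 0.632} = Φ(1.456) ≈ 0.927.

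The stated 90% is met without any adjustment.

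**Step 3: what adjustment adds.** Simulation, 6,000 trials per row, 240 women, arms balanced within two centres, true adherence 80% versus 60% (or 60% in both arms under the null). Chi-square is compared with logistic regression on arm, centre and baseline SMAQ. The following are assumptions, because the protocol gives no values: baseline adherence 60%, centres split 70:30, centre odds ratio 1.5, and the baseline-to-Month-12 odds ratio in the first column.

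| Assumed baseline OR | Power, chi-square | Power, adjusted | Gain (points) | Type I error if either test could count |
|---|---|---|---|---|
| 1 | 92.8% | 92.9% | 0.1 | 5.0% |
| 3 | 92.7% | 93.9% | 1.2 | 6.1% |
| 6 | 93.2% | 96.0% | 2.8 | 7.3% |
| 10 | 92.8% | 97.2% | 4.4 | 7.1% |

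Under the null each test alone rejects in 4.7% to 5.5% of trials (Monte Carlo standard error about 0.3 points). A rerun with 20,000 trials per row gave the same pattern: chi-square about 93%, adjusted 93% to 97%, either test 5.4% to 7.4%. In the first row baseline carries no information, so the row isolates centre. At the assumed odds ratio of 1.5, centre adds essentially nothing to power, and the gain comes from baseline SMAQ.

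A second simulation used 126 per arm, baseline adherence 65% and stronger baseline coefficients (log-odds 1.5 to 3.0, that is odds ratios of about 4.5 to 20). It put the either-test error at 6.1% to 7.8%. Across both simulations the range is about 5% to 8%.

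**Step 4: the odds ratio changes meaning.** The unadjusted odds ratio for 80% versus 60% is (0.80/0.20) / (0.60/0.40) = 2.67. In the simulated models the treatment odds ratio conditional on baseline and centre was 2.68, 2.86, 3.18 and 3.58 for the four rows. The risk difference averaged over the study population stays at 20 points throughout.

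**The case against.** The strongest reply is that the plan is already adequate. The chi-square is valid after stratified randomisation, it meets the stated power, and the abstract's word order and the sample size calculation both point to it as the main test. Covariate lists commonly sit in a statistical analysis plan that is not shown, and unnamed confounders do not exclude centre. The abstract does put a baseline covariate in the logistic model. All of this stands, and it makes the point an improvement rather than a fault. It does not remove the mismatch between the abstract and the body text, or the absence of a sentence ranking the two results.

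A reader might infer more than the document supports:

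- **Two decisive tests that inflate type I error.** No rule lets either test declare success. The 5% to 8% is what would follow from such a rule, not a property of the plan.
- **An underpowered trial.** A chi-square power of about 73% arises only at 75% versus 60% with 126 per arm, which is not the planned effect.
- **Month-6 SMAQ wrongly ignored.** It is measured after randomisation and may be affected by the reminders, so it should not be a covariate for the Month-12 effect.
- **Dropouts excluded despite the intention-to-treat label.** No sentence restricts the analysis to women with a Month-12 value, and missing-data rules are commonly left to the analysis plan.
- **Confidence intervals too wide.** Adjusting a logistic model for a prognostic covariate does not in general shrink the standard error of the log odds ratio. Power rises because the conditional odds ratio lies further from 1.

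**Conclusion.** The point holds as a low-cost improvement to the analysis. The planned test is valid and sufficiently powered under the protocol's own assumptions. Its limits are that it leaves baseline SMAQ unused, leaves the design stratum out, and sits beside a second analysis with unnamed covariates and no stated rank.

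The gain from the adjusted model is about 0 to 4 points of power at 80% versus 60% with 120 per arm, from about 93% to between 93% and roughly 97%. Where it falls in that range depends on how strongly baseline SMAQ predicts Month-12 SMAQ, which the protocol does not say. Naming one decisive analysis in advance is useful whatever that strength is. The difference between the abstract and the body text on baseline adjustment is in the document itself and needs reconciling.

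**What to change.** - Name one primary analysis: logistic regression of Month-12 SMAQ adherence on arm, centre and baseline SMAQ, reported as a standardised risk difference and an odds ratio, each with a 95% CI.
- Label the unadjusted chi-square as supportive.
- Make the abstract and the Statistical analysis plan section state the same covariates for the primary endpoint.
- Add centre to the hormone and questionnaire models.
- Do not use Month-6 SMAQ as a covariate. Missing-data detail can stay in the statistical analysis plan.

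The cost is wording and a little programming, since centre is recorded at randomisation and baseline SMAQ is already scheduled. The change should be made before any outcome data by arm are examined. The one small drawback is that the adjusted odds ratio is conditional and will differ from the unadjusted one (Step 4). Reporting the standardised risk difference alongside it handles this.

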**Methods/Design:**

In this randomised controlled trial, eligible patients will be equally allocated to receive either SMS reminder or standard care. The former receives weekly SMS reminder to take medication while the latter does not receive any. The primary endpoint of medication adherence at 1-year is assessed using the Simplified Medication Adherence Questionnaire, and compared using the χ^2^ test. Adjustment for baseline covariate and potential confounders will be made using the logistic regression. Secondary outcomes involving estrone and androstenedione levels will be compared using the analysis of covariance, whereas the estradiol levels (< 18.4 pmol/L versus ≥18.4 pmol/L) will be compared using the χ^2^ test, and the logistic regression. Further, the assessment of knowledge, attitude, behaviour, and barriers and facilitating factors of medication adherence will be made via logistic regression.

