### Barriers and facilitating factors influencing medication adherence

Malcolm et al. identified cost, side-effects, transportation, lack of reimbursement for the medication and inefficient patient-physician communication as barriers to medication adherence [25]. Medication-taking behaviour has been shown to be influenced by a patient’s belief and his/her trust in the physician who prescribes the medication [26]. Also, non-adherence to endocrine therapy might be due to patients’ response to the AI therapy and its associated side effects such as arthralgia [27]. Besides, it has been shown that nonadherence to medications for chronic diseases prior to hormonal therapy was associated with more severe nonadherence to oral hormonal therapy in patients with breast cancer [28] A cross-sectional study comprising mostly White women showed that survivors who perceived that their pain made taking AIs difficult or that the AI treatment lasted too long were likely to be non-adherent, as assessed by the Health Beliefs Scale Items and Scale Properties [29]. In contrast, a systematic review showed that taking more medications at baseline, referral to an oncologist, and being diagnosed at earlier times were positively associated with adherence and/or persistence [16]. Thus, in non-adherent patients, it is desirable to understand their attitude and perception towards medication taking.

Cancer treatment adherence plays a crucial role in optimising health outcomes while medication non-adherence is associated with decreased survival, higher recurrences and increased healthcare costs. Hsieh et al. reported that interruption and non-adherence to long-term adjuvant hormone therapy was associated with increased mortality in breast cancer women [30]. Treatment non-adherence to adjuvant hormonal therapy was found to be associated with increased all-cause mortality amongst Asian breast cancer women. Moreover, a greater impact of non-adherence on mortality was especially found in the younger breast cancer population [30].

Implementing innovative technology to tackle the problem of non-adherence and understanding its barriers will provide scientific evidence for clinical decision making and improve health outcomes. We thus propose to examine the effect of a computer automated SMS reminder in improving medication adherence amongst breast cancer women receiving oral AI therapy.

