### Study objectives

The primary objective is to evaluate whether SMS reminder improves medication adherence as compared to standard care (control) amongst breast cancer women who have been receiving adjuvant endocrine therapy for at least 1 year, and are continuing to receive adjuvant AI therapy for at least 1 more year.

The secondary objectives are to examine whether SMS reminder improves the inhibition of aromatisation process of patients receiving AI therapy. We postulate that at 1-year, there will beLower estrone and estradiol levels in the SMS reminder group as compared to the control.Higher androstenedione level in the SMS reminder group as compared to the control.

Tertiary objectives includeAssessing the impact of SMS reminder on the improvement in knowledge, attitude and behaviour towards medication compliance.Identifying barriers and facilitating factors for medication adherence.

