In short, sending SMS reminder to early-stage breast cancer women could be an added feature to existing healthcare protocol for breast cancer women if the results from our trial are promising. Understanding the potential barriers to medication adherence would enable policy makers to make informed decision when promoting regulations to minimise the impact of the barriers while formulating policies to elevate medication adherence.

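### One between-arm analysis is assigned to two tertiary objectives; it suits the effect of SMS on knowledge, attitude and behaviour but not the identification of barriers and facilitators of adherence

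*Protocol article*

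**What the plan says.** The Study objectives section of the protocol article gives two tertiary objectives. The first is the impact of the SMS reminder on knowledge, attitude and behaviour. The second is "Identifying barriers and facilitating factors for medication adherence".

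The Statistical analysis plan section handles both in one short paragraph. It puts the two objectives under a single χ² comparison, in these words: "as well as barrier and facilitating factors between the intervention and control groups will be made using". Each such comparison is to be reported "with treatment effect quantified based on odds ratio estimate and its 95% confidence interval". Logistic regression comes in afterwards: "Further adjustment for baseline scores and other potential confounders will be made using the logistic regression analysis where appropriate".

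The abstract is worded differently. Its sentence on the tertiary outcomes ends: "barriers and facilitating factors of medication adherence will be made via logistic regression".

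Two other places show what the second objective is for. The background section on barriers says that "in non-adherent patients, it is desirable to understand their attitude and perception towards medication taking". The Discussion closes with: "Understanding the potential barriers to medication adherence would enable policy makers to make informed decision".

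**The concern.** The two tertiary objectives are different questions. The first asks what the intervention does to beliefs and behaviour, and a comparison of randomised arms answers it. The second asks which factors go with taking or not taking the medication. That needs adherence on one side of the analysis and the candidate factors on the other.

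The paragraph gives the second question the analysis of the first. Followed literally, the report would hold a table of arm differences in each factor under a heading about barriers to adherence. A factor strongly tied to non-adherence but untouched by a weekly text message would look unimportant. A factor that the message shifts, but that has no bearing on adherence, would look important. Neither the background's interest in non-adherent patients nor the Discussion's remark on policy could rest on such a table.

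**Working it through.** No figure in the document is in dispute. The check sets the texts side by side, illustrates the consequence, and then asks what data the right analysis would have.

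**1. Objective against analysis**

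| Element | Knowledge, attitude, behaviour | Barriers and facilitators |
|---|---|---|
| Question (Study objectives) | Effect of SMS on the factor | Relation of the factor to adherence |
| Outcome needed | The factor at 1 year | Adherence |
| Explanatory variable needed | Randomised arm | The factor |
| Analysis stated (Statistical analysis plan) | Factor by arm, χ², treatment-effect odds ratio | The same |
| Match | Yes | No |

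The logistic regression in that section only adjusts the arm comparison. The section on assessing medication adherence describes a sub-study that compares adherence measures with one another, so it does not supply the missing link either.

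**2. Which time point is compared**

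The paragraph adjusts for baseline scores, and the Follow-up and assessments section states: "The SMAQ will be administered at each visit, while the BMQ and ASK-12 questionnaires will be administered at baseline and 1-year". The comparison is therefore most naturally of 1-year values. It estimates the effect of SMS on the factor, which is a valid quantity but not the one this objective asks for.

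**3. Illustration under assumed values**

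Inputs from the document: 120 per arm, two-sided 5% level, adherence of about 60% (control) and 80% (SMS). Assumed, not from the document: a yes/no factor, its prevalence, and its odds ratio with adherence. There were 4,000 simulated trials, with uncorrected χ² tests.

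- *Factor present in 40% of both arms, odds ratio with adherence 0.33.* The arm comparison is significant in 5.6% of trials; a test of factor against adherence is significant in 96%.
- *Factor unrelated to adherence within arm (odds ratio 1), present in 40% of controls and 20% of the SMS arm.* The arm comparison is significant in 93%. This agrees with the calculated power of 0.927 for 80% versus 60% at 120 per arm, because 20% versus 40% is the same contrast seen from the other side. The crude test of factor against adherence is significant in 11.5%, above 5%, because arm affects both. A model for this objective should therefore include arm.

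**4. Data available for the matching analysis**

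- The plan's minimum of 240 is reproduced closely: 80% versus 60%, two-sided 5%, 90% power gives 109 per arm without continuity correction and 119 with it (238 in all).
- Evaluable women: 280 × (1 − 0.10) = 252, or 126 per arm.
- Non-adherent: 126 × 0.20 + 126 × 0.40 = 25.2 + 50.4 = 75.6, about 76.
- Pooled rate: 75.6 / 252 = 30%.

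About 76 events, with three terms already taken by arm, centre (two sites) and baseline SMAQ, leave room for a short list of factors only.

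**The case against.** The strongest reply is the abstract. It speaks of factors of medication adherence and of logistic regression, and does not mention the arms. That fits a regression of adherence on the factors, and the one sentence in the analysis section may simply be a condensation of two analyses. Part of this stands: the intention may well have been right, and a predictor list or model form is properly left to a fuller document. But the abstract names no outcome and no predictors. Its sentence also covers knowledge, attitude and behaviour, for which the arm comparison is the natural analysis, so it merges the two objectives as well. If a regression on adherence was meant, the analysis section says something else and the two need aligning. The point is that an analysis is stated and does not fit, not that detail is absent.

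Three stronger readings are tempting and not supported.

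- A reader might infer that the planned odds ratio is 1.0 by randomisation, so that the test can find only false positives. That holds for baseline factors. The adjustment for baseline scores points to 1-year values, where SMS may produce a real difference.
- A reader might infer that the trial cannot answer the objective. It can: SMAQ, BMQ and ASK-12 are all collected at baseline and 1 year. Only the stated analysis fails.
- A reader might infer that a planned policy inference is compromised. The Discussion's remark is general and is not a planned inference.

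It is also fair to say that baseline factors do not guarantee the right time order. Women enter after at least 1 year of endocrine therapy, so their beliefs at entry may reflect earlier adherence. This is why baseline SMAQ belongs in the model and why the result should be called associational.

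**Conclusion.** Wrong as written, at low severity. The analysis section gives the objective on barriers and facilitators a comparison that answers the other tertiary objective, and the abstract does not repair this. The conclusion rests on the text and needs no numerical assumption. The simulated percentages only illustrate it and depend on assumed prevalences and odds ratios. The figure of about 76 non-adherent women of 252 depends on the planned 80% and 60% adherence and 10% attrition. Sample size, primary analysis and secondary analyses are untouched.

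**What to change.** In the Statistical analysis plan section, separate the two tertiary objectives.

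- **Knowledge, attitude and behaviour:** keep the between-arm comparison as stated.
- **Barriers and facilitators:** state a logistic regression of Month-12 SMAQ adherence (yes/no) in all randomised women with that outcome. Explanatory variables are a short prespecified list, such as baseline BMQ and ASK-12 scores and a few key demographic or clinical variables, with arm, centre and baseline SMAQ as covariates. Label it exploratory and associational.
- Keep the list short enough for about 76 events.
- Word the abstract's sentence to match.

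The cost is a few sentences. No new data, visits or participants are needed.

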### Data collection

Three questionnaires will be administered via face-to-face interview by the Research coordinator. The Simplified Medication Adherence Questionnaire (SMAQ) is a validated 6-item questionnaire which measures adherence [32]. Non-compliance is defined if a patient responds to any of items 1 to 4 with a non-adherence answer; and if the patient has skipped more than two doses during the last week or has not taken medication for more than two complete days during the last visit. In addition, information on knowledge, attitude and behaviour towards medication taking will be elicited via the Beliefs about Medicines Questionnaire (BMQ) [33] and the Adherence Starts with Knowledge (ASK-12) questionnaire [34].

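### The tertiary BMQ and ASK-12 outcomes are planned as categorical comparisons, which gives up precision that ANCOVA on the scores would keep

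*Protocol article*

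**What the plan says.** All references are to the protocol article.

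- **Study objectives** places the effect of the reminder on improvement in knowledge, attitude and behaviour among the tertiary objectives.
- **Data collection** assigns these domains to the BMQ and ASK-12. **Follow-up and assessments** gives the timing: "BMQ and ASK-12 questionnaires will be administered at baseline and 1-year".
- **Statistical analysis plan** compares these domains, together with barriers and facilitating factors, by χ² tests, "with treatment effect quantified based on odds ratio estimate and its 95% confidence interval". The next sentence reads: "Further adjustment for baseline scores and other potential confounders will be made using the logistic regression analysis where appropriate". The abstract also names logistic regression for this assessment.
- For two of the hormones, the same section says that the comparison of "estrone and androstenedione levels will be made using the analysis of covariance (ANCOVA) to adjust for the respective baseline levels" and for other potential confounders.
- Where the section does split a measured quantity, it gives the threshold: "The estradiol levels (defined as < 18.4 pmol/L versus ≥18.4 pmol/L) will be compared between the two arms".
- All tests are made "assuming a two-sided test at the 5% level of significance".

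**The concern.** The section calls the baseline questionnaire measures scores, yet every method it names for the follow-up comparison needs a categorical outcome. The natural reading is that 1-year scores are reduced to categories before the arms are compared. This treats all participants within a category as alike. In addition, the χ² test makes no use of the baseline score, which enters only in a further logistic adjustment made where appropriate.

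The section already uses the more precise method for two outcomes measured at the same two visits, and gives no reason for treating the questionnaires differently. At stake is the chance of seeing a real shift in beliefs or behaviour, and the width of the interval around it.

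**Working it through.** **1. The plan's own figures.** The article gives no power or precision figure for the BMQ or ASK-12. Its only sample size is for the primary endpoint: 80% versus 60%, two-sided 5%, power 90%, 120 per arm.

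- Without continuity correction: n = [1.96·√(2·0.7·0.3) + 1.2816·√(0.8·0.2 + 0.6·0.4)]² / 0.2² = (1.270 + 0.811)² / 0.04 ≈ 108.2, so 109 per arm.
- With continuity correction: 119 per arm (238 in total), which agrees with the stated 120 and 240.

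I therefore use 120 evaluable per arm below.

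**2. Assumptions not in the article.** 1-year scores are normal with SD 1; the cut lies at the median or the 80th percentile; the baseline to 1-year correlation r is 0 to 0.7.

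**3. Unadjusted χ² test relative to ANCOVA.** For a cut at quantile p, with c the normal quantile and φ the normal density, the information kept relative to a t-test is φ(c)² / [p(1−p)].

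- Median: 0.3989² / 0.25 = 2/π = 0.637.
- 80th percentile: 0.2800² / 0.16 = 0.490.

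ANCOVA reduces the variance by the factor 1 − r², so the information kept relative to ANCOVA is that figure times (1 − r²). At the median with r = 0.5: 0.637 × 0.75 = 0.477.

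**4. Baseline-adjusted logistic model relative to ANCOVA.** This was simulated: 600 replicates per setting, 120 per arm, true difference 0.36 SD, and the ratio of squared mean z-statistics. The same runs reproduced the χ² values of step 3 to within 0.024, so the logistic figures should be read to about that accuracy.

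Information kept relative to ANCOVA:

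| Analysis | Cut | r = 0 | r = 0.3 | r = 0.5 | r = 0.7 |
|---|---|---|---|---|---|
| χ², unadjusted (formula) | median | 0.637 | 0.579 | 0.477 | 0.325 |
| χ², unadjusted (formula) | 80th percentile | 0.490 | 0.446 | 0.367 | 0.250 |
| Logistic, adjusted (simulated) | median | 0.648 | 0.630 | 0.518 | 0.454 |
| Logistic, adjusted (simulated) | 80th percentile | 0.455 | 0.466 | 0.399 | 0.339 |

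The loss is therefore 36% to 75% for the χ² test (1 − 0.637 to 1 − 0.250) and 35% to 66% for the logistic model (1 − 0.648 to 1 − 0.339). Baseline adjustment recovers part of the loss when r is high, but does not undo the effect of categorising.

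**5. What this means for power.** For illustration: 120 per arm, median split, r = 0.5.

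| Assumed difference (SD) | ANCOVA | χ² |
|---|---|---|
| 0.30 | 76.5% | 45.5% |
| 0.36 | 89.6% | 60.1% |
| 0.40 | 94.7% | 69.2% |
| 0.50 | 99.4% | 86.9% |

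These are formula values. At 0.36 SD the simulation gave 88% for ANCOVA, 63% for adjusted logistic regression and 56% for χ².

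**The case against.** **The text does not say that total scores are cut.** The analysis sentence does not name the BMQ or ASK-12 and mentions no split. Item-level responses would also suit a χ² test, especially for barriers and facilitating factors. This stands as a caution: categorisation of the scores is an inference, though a strong one given the reference to baseline scores and the odds ratio.

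**Missing cut-points.** A reader might infer that the threshold is open and could be chosen after seeing the data, since estradiol has one and the questionnaires do not. The article does not support that. It condenses a fuller protocol, and category definitions may sit there or in an analysis plan not shown. The point rests on the stated method, not on the absent threshold.

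**Validity.** A reader might infer that a χ² test at 1 year cannot address improvement because it ignores baseline. Under 1:1 randomisation a between-arm comparison at 1 year is a valid comparison of the arms, and ANCOVA also compares 1-year values. The planned logistic model does provide for baseline adjustment. The difference is one of precision.

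**Importance.** These are tertiary outcomes for which the article claims no power. That stands and limits the severity.

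**Conclusion.** The point holds as one of efficiency. The article commits the BMQ and ASK-12 outcomes to categorical methods, while ANCOVA on the scores, already used for two hormones, was more precise in every setting tried.

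The loss is roughly one third to three quarters for the χ² test and about 35% to 66% for the adjusted logistic model. Both ranges assume normal scores, a cut between the median and the 80th percentile, and r from 0 to 0.7. It would be tempting to say that half the information is lost, but that fits only particular settings, such as a median split with r near 0.5, and cannot be stated as a property of this trial. Markedly non-normal scores would give other figures.

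Severity is low. The comparison is valid, and the primary analysis, sample size and hormone analyses are unaffected.

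**What to change.** In the Statistical analysis plan section, and in the matching sentence of the abstract:

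- Analyse the 1-year BMQ and ASK-12 scores by ANCOVA with arm, centre (the stratification factor under Randomisation procedure) and the corresponding baseline score. Report the adjusted mean difference with its 95% confidence interval.
- Keep any categorised analysis of these scores as supportive.
- Keep χ² tests and logistic regression for barrier and facilitator items that are truly categorical, and state which items these are.

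The cost is a change of wording. Both instruments are already given at baseline and 1 year, so no new data, visits or participants are needed. The one small downside is that the effect measure becomes a mean difference on the score scale instead of an odds ratio.
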